## Methodology of statistical analysis

The characteristics of the patients in the two study groups will be described (applying the appropriate estimators according to the type of variables, such as means and confidence intervals, medians and interquartile ranges or proportions) and possible differences between the groups will be assessed using appropriate statistical tests of differences of means, distributions of ranks or proportions. The comparison of the primary variable and the secondary variables of the study in both groups at baseline, at four months and 10 months after the start of rehabilitation will be carried out using Pearson χ2 test for qualitative variables (Fisher exact test for dichotomous variable) or Student t-test for independent samples for quantitative variables (Mann-Whitney U test when parametric assumptions couldn’t be assumed). The treatment effects within groups (at four months or ten months) will be assessed using McNemar-Bowker test of symmetry for qualitative variables (McNemar test for dichotomous variable) or Student t-test for paired samples for quantitative variables (Wilcoxon signed-rank test when parametric assumptions couldn’t be assumed). The relationship between quantitative variables will be assessed by Pearson’s correlation coefficient (Spearman’s rank correlation coefficient when parametric assumptions couldn’t be assumed). Multiple linear regression models will be used to assess the significance and magnitude of the intervention effect controlling for possible differences in patient characteristics between groups. In general, backward-forward models will be used, initially constructing the complete models and excluding non-significant variables one at a time (p for variable removal: 0.10) but trying to include the previously removed variables after each exclusion (p for incorporation: 0.05. The analysis will be performed on an intention-to-treat basis. For the economic evaluation, the unit cost will be obtained by quantifying the consumption of resources and applying the official cost rates of the Valencian Health Agency or, if these are not available, they will be estimated by assessing the time and cost of the resources involved. Two-sided exact p-values will be calculated whenever possible and p-values ≤ 0.05 were considered statistically significant. Data will be analysed using IBM SPSS Statistics 22 and R 4.0.2 for Microsoft Windows.

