## Secondary Objectives

Verify the improvement of the following parameters after the intervention:

A. Stress test:

● Demonstrate increase in VO2max.

● Demonstrate increase in exertion time.

● Demonstrate increase in workload.

● Decrease the presence of symptoms.

B. Analytical:

● Obtain improvement in lipid profile.

● Decrease in CRPus.

C. Lifestyle:

● Demonstrate increased adherence to Mediterranean diet.

● Demonstrate improved outcomes in psychological state.

● Demonstrate increased willingness to quit smoking and smoking cessation.

● Demonstrate a decrease in the sedentary lifestyle indicator.

● Demonstrate an earlier return to work.

D. Arterial stiffness

Improving carotid-femoral pulse wave velocity measurement

E. Socio-economic variables

To evaluate the cost per patient/month in the control cases of conventional rehabilitation and extended tele-rehabilitation intervention.

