## Description of the randomisation process

After agreeing to participate in the study, subjects will be assigned to follow the conventional rehabilitation or telerehabilitation program, according to a block randomisation, estimated using a conventional statistical program.

Subject eligibility will be established prior to allocation to rehabilitation type and inclusion will be sequential. If a subject withdraws from the study his/her randomisation number will not be re-used and re-entry into the study will not be allowed.

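### Baseline activity is not secured in any between-arm analysis, no analysis is named primary, and within-arm pre-post tests are presented as treatment effects

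*Protocol*

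**What the plan says.** Section 9.3 (repeated in the summary's Data Analysis section) describes three kinds of analysis and ranks none of them.

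- **Between arms, visit by visit.** "The comparison of the primary variable and the secondary variables of the study in both groups at baseline, at four months and 10 months" uses, for quantitative variables, the "Student t-test for independent samples for quantitative variables (Mann-Whitney U test when parametric assumptions couldn’t be assumed"). No baseline covariate enters this comparison.
- **Within each arm.** "The treatment effects within groups (at four months or ten months) will be assessed using McNemar-Bowker test of symmetry for qualitative variables", with paired t or Wilcoxon tests for quantitative variables.
- **Regression.** "Multiple linear regression models will be used to assess the significance and magnitude of the intervention effect controlling for possible differences in patient characteristics". Terms are chosen by backward-forward selection, "excluding non-significant variables one at a time (p for variable removal: 0.10") and re-entering them at p 0.05. Baseline IPAQ is not named, and no term is stated as forced in.

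The primary variable is METs-minutes/week from the IPAQ (section 7.3), and the baseline IPAQ is on the Visit 1 form in Annex 1. The general objective in the summary is comparative. The version in section 4.1 drops the comparator, and section 4.2 introduces the secondary objectives with "Verify the improvement of the following parameters after the intervention", naming no comparator in that lead-in.

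**The concern.** Two separate weaknesses sit in the same paragraph.

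The first is precision and prespecification. The trial has 60 patients. The baseline value of the primary outcome is available at no cost, yet the stated comparison does not use it. The only analysis that could use it leaves its inclusion to a p-value rule. With no analysis named primary, the t-test, the Mann-Whitney test and the selected regression could give different answers, and nothing says which one counts.

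The second is interpretation. A pre-post change in one arm is not a treatment effect. Baseline surveys follow a stress test done 7 to 10 days after discharge (section 6.4), and the IPAQ asks about the previous 7 days (section 7.2). The reference week is therefore early convalescence after an acute coronary syndrome. Both arms then receive active rehabilitation (section 6.2). A rise in both arms is plausible whether or not telerehabilitation is better, and a within-arm test would credit that rise to the programme. Objectives worded as improvement without a comparator leave room for that reading.

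**Working it through.** **Inputs from the protocol (section 9.1):** two-sided alpha 0.05, 27 per arm, means 5000 and 4000 (difference 1000), stated power 95%. **Not given:** the SD, the baseline-to-10-month correlation r, and the expected rise common to both arms. These three are assumptions below.

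**1. The plan's own figure.** Without an SD, the 95% cannot be reproduced from the stated inputs alone. Solving the two-sample t power for the SD gives about 1000 (normal approximation: 1019). Check at SD 1000: noncentrality = 1000 / (1000 × √(2/27)) = 1 / 0.272 = 3.67, and power on 52 degrees of freedom is 95.0%. So SD 1000 is the implied value, and larger SDs are shown as a range.

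**2. Gain from forcing in baseline.** Residual SD under ANCOVA = SD × √(1 − r²), with 51 degrees of freedom. The multiplier is 0.954, 0.866 and 0.714 for r = 0.3, 0.5 and 0.7.

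| Assumed SD | Unadjusted | r = 0.3 | r = 0.5 | r = 0.7 |
|---|---|---|---|---|
| 1000 | 95.0% | 96.5% | 98.6% | 99.9% |
| 1500 | 67% | 71% | 79% | 92% |
| 2000 | 44% | 47% | 55% | 71% |

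In sample-size terms, 27 / (1 − r²) = 30, 36 and 53 unadjusted patients per arm. At r = 0.1 the gain is below half a point at each of the three SDs (for example 67.2% to 67.6% at SD 1500). A low r is possible because the baseline week is convalescence.

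**3. Would stepwise selection keep baseline?** I simulated 54 patients in a model with arm and baseline only. At a true r of 0.3, baseline fails the 0.10 threshold in about 28% of trials; at r = 0.5, in about 1%. Selection thus tends to lose baseline when its correlation is modest. The fuller model in the protocol, with other covariates competing, is not specified enough to simulate.

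**4. What a within-arm test shows when the arms do not differ.** Suppose both arms rise by the same amount. SD of change = SD × √(2(1 − r)), which equals SD when r = 0.5. The paired t-test with n = 27 has noncentrality (rise / SD of change) × √27. The chance that exactly one arm is significant is 2p(1 − p), the arms being independent.

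| Common rise, in SDs of change | Chance a given arm is significant | Chance exactly one arm is significant |
|---|---|---|
| 0.2 | 17% | 28% |
| 0.5 | 71% | 2 × 0.706 × 0.294 = 42% |
| 0.8 | 98% | 4% |
| 1.0 | 99.9% | 0.2% |

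At SD 1000 and r = 0.5, the 0.5 row is a rise of 500 METs-minutes/week and the 1.0 row a rise of 1000. The middle column carries the point: a significant improvement within the telerehabilitation arm can be likely, even near certain, with no advantage over conventional rehabilitation. The discordance in the last column depends strongly on the size of the common rise.

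**The case against.** Several stronger readings are tempting, and the documents do not support them.

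- **That the baseline IPAQ is wasted.** Section 9.3 plans a regression for the intervention effect that could include it, and the paired tests use it. The accurate fault is that its inclusion is not secured. Exact covariates are often left to a statistical analysis plan, which is not shown here. The stepwise rule, however, is fixed in the protocol itself.
- **That recovery biases the main comparison.** It does not. Recovery shared by randomised arms cancels in the 10-month between-arm test. ANCOVA buys precision and removes chance baseline imbalance from the estimate; it does not repair an invalid test.
- **That the protocol plans to declare benefit from within-arm p-values.** No text says so. The summary's general objective is relative to conventional rehabilitation, section 9.1 powers a difference between arms, and section 9.3 compares the secondary variables between arms too. The risk comes from the treatment-effect label and from the lead-in to section 4.2.
- **That a large loss of power is shown.** At the SD implied by the protocol's own 95%, the gain is only 1.5 to 4.9 points. It matters only if the true SD is larger.
- **That the randomisation is at fault for not stratifying.** Section 9.2 states allocation "according to a block randomisation, estimated using a conventional statistical program" and mentions no stratification by hospital. Stratifying 60 patients is optional, and the protocol does not give the split of recruitment between hospitals, so the risk of imbalance cannot be sized from it.

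What stands is that baseline is unprotected, the primary analysis is unnamed, and the within-arm tests carry the wrong label.

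**Conclusion.** The point holds in this limited form and should be corrected, although it does not invalidate the trial. The 10-month between-arm comparison is sound but may be less precise than the collected data allow. The size of the loss rests on an assumed SD and r: a few points of power at SD 1000, and up to 25 points at SD 1500 (67% to 92%) or 28 at SD 2000 (44% to 71%, both at r = 0.7). It is close to nothing if r is near 0.1. The labelling fault does not depend on those figures: a paired test inside one arm cannot identify a telerehabilitation effect when both arms are recovering and both are being rehabilitated. The percentages attached to it do depend on the assumed common rise.

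**What to change.** - Name one primary analysis: the between-arm difference in 10-month METs-minutes/week by ANCOVA, with arm and baseline METs-minutes/week forced in, reported with a 95% confidence interval. Recruiting hospital may be added as a covariate. Give a log or rank version as a sensitivity analysis for skew.
- Use the same model for each continuous secondary outcome that has a baseline value.
- Drop stepwise selection for the treatment effect.
- Report within-arm changes descriptively, without p-values and without calling them treatment effects.
- Word the objectives in sections 4.1 and 4.2 as telerehabilitation versus conventional rehabilitation.

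The cost is a wording change in the protocol and analysis plan and about one or two degrees of freedom. No additional data are needed, because the IPAQ is already on the baseline and month-10 forms.

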## Population under study and total number of subjects

The study population consists of men and women with a maximum age of 72 years diagnosed with acute coronary syndrome who will be enrolled in a cardiac rehabilitation program. Sixty patients will be included in two groups of 30 subjects assigned to each rehabilitation program.

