# Statistical Analysis

## Sample size calculation

## The sample size is determined by the number of patients eligible for inclusion in the study who are seen in each hospital during the inclusion period. Thirty patients will be included in each of the following groups: control group, conventional rehabilitation group and telerehabilitation group. For the calculation of the power of the study, a 12% possible loss to follow-up has been estimated. Thus, accepting an alpha risk of 0.05 in a bilateral test with 27 subjects in the control group and 27 patients in the intervention group, the power of the hypothesis test is 95% to detect as statistically significant the difference between the mean of 5000 in the first group and the mean of 4000 in the second group after rehabilitation. Based on the potential impact of the telerehabilitation intervention on compliance with the physical activity recommendation at 10 months follow-up, and considering METs-minutes/week as the unit of measurement, it has been estimated that patients in the intervention group will perform 5000 METs-minutes/week while in the conventional rehabilitation group they will perform 4000 METs-minutes/week. It is estimated that physical activity in the non-rehabilitation group will be significantly lower.

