**SOCIO-OCCUPATIONAL SITUATION**

| Active worker (Y/N) |  |
| --- | --- |
| Time to return to work after discharge (días) |  |

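### Fisher's exact test, fixed for the secondary between-arm yes/no comparisons, is valid but conservative at 27 to 30 per arm; Boschloo's exact test would recover some power under the same 5% limit

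*Protocol*

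**What the plan says.** Protocol section 9.3 (Methodology of statistical analysis), repeated in section 1.15 (Data Analysis), compares the arms at baseline, 4 months and 10 months. Qualitative variables get Pearson's chi-square, with the "Fisher exact test for dichotomous variable". No condition on expected counts is attached, so Fisher's test applies to every two-category between-arm comparison. Within-arm changes use a different test, the "McNemar test for dichotomous variable".

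The same section adds: "Two-sided exact p-values will be calculated whenever possible and p-values ≤ 0.05 were considered statistically significant". It names SPSS 22 and R 4.0.2 as software.

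On numbers, section 1.12 states: "Sixty patients will be included in two groups of 30 subjects assigned to each rehabilitation program". Section 9.1 allows 12% loss and bases power on a comparison "with 27 subjects in the control group and 27 patients in the intervention group".

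The yes/no items on the month-10 form (Annex 1, Visit 3) are ST descent, angor, emergency consultation, hospitalisation, revascularisation and active-worker status. The principal variable (section 7.3) is METs-minutes/week, which is quantitative.

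**The concern.** Fisher's test fixes both margins of the 2x2 table. In small arms few tables are then possible, and the p-value moves in large steps. The test keeps its 5% limit by stopping well short of it. The plan has already decided to use exact p-values, so the real choice is between exact tests, and another exact test gives the same guarantee while rejecting in more tables.

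At stake is power for secondary yes/no outcomes in a 60-patient trial, where it is already modest. Some of these outcomes serve stated objectives, such as the reduction of symptoms on the stress test.

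**Working it through.** **The plan's own figure.** The only power stated is 95% for means of 5000 v 4000 METs-minutes/week with 27 per arm. No SD is given. Solving backwards with the t-test, 95% requires an SD of about 1000. That calculation concerns the quantitative primary variable and does not involve Fisher's test. The protocol states no event rate, error rate or power for any yes/no outcome, so there is nothing further to reproduce.

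**Inputs.** 30 per arm randomised (section 1.12); 27 per arm analysed (section 9.1; 30 × 0.88 = 26.4); two-sided 0.05 (section 9.3). Event rates are assumptions.

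**Definitions.** Let x of n1 and y of n2 be the event counts and b the binomial probability.
- Fisher p: given the total x + y, the sum of hypergeometric probabilities no larger than that of the observed table.
- Boschloo p: the maximum over a common rate π of P(Fisher p ≤ observed Fisher p).
- True size at π: the sum of b(x; n1, π) · b(y; n2, π) over all tables with p ≤ 0.05. Power uses π1 and π2 in place of π.

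**Why Boschloo cannot do worse.** Within each total, P(Fisher p ≤ f) ≤ f. Averaging over totals gives P(Fisher p ≤ f) ≤ f for every π. So Boschloo's p never exceeds Fisher's p.

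**A table that can be checked by hand.** Take 0/27 v 5/27. Fisher p = 2 × C(27,5)/C(54,5) = 2 × 80,730/3,162,510 = 0.051, not significant. Boschloo's p for the same table, by enumeration, is 0.026.

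**Size at 27 v 27**, all 28 × 28 tables enumerated:

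| Common rate | Fisher | Boschloo |
|---|---|---|
| 10% | 0.73% | 2.19% |
| 20% | 1.91% | 4.08% |
| 30% | 2.51% | 4.45% |
| 50% | 2.16% | 4.06% |
| Maximum over all rates | 2.63% | 4.46% |

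At a 5% rate Fisher's size is 0.10%. Fisher rejects in 424 tables; Boschloo rejects in the same 424 and 36 more.

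**Power at 27 v 27, assumed rates:**

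| Rates | Fisher | Boschloo | Gain (points) |
|---|---|---|---|
| 10% v 40% | 63.2% | 73.5% | 10.3 |
| 20% v 50% | 55.0% | 62.7% | 7.7 |
| 30% v 60% | 48.1% | 57.8% | 9.7 |
| 30% v 65% | 62.6% | 72.0% | 9.4 |

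In the same four scenarios the gain is about 7 to 10 points at 26 v 26 and 3.8 to 8.6 at 30 v 30. Fisher's maximum size is about 2.8% and 2.7% respectively.

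**Unequal arms, same four scenarios:**

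| Arms | Fisher maximum size | Gain (points) |
|---|---|---|
| 26 v 27 | 3.6% | about 3 to 5.6 |
| 29 v 30 | 3.6% | 0.7 to 4.8 |
| 28 v 30 | 3.7% | 1.8 to 4.7 |
| 26 v 28 | 3.6% | 4.4 to 9.1 |

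At 25 v 27 Fisher's maximum size is 3.9%. At 25 v 28 some gains are below 1 point. In every split run, Boschloo's region contained Fisher's and its maximum size stayed below 5%.

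**The case against.** The strongest reply is that nothing here is wrong. Fisher's test is standard, prespecified, holds the 5% limit and agrees with the plan's own rule that "Two-sided exact p-values will be calculated whenever possible". Preferring another valid exact test is a matter of efficiency. That stands, and it limits how much weight the point can carry.

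The size of the gain is also fragile. It is largest with exactly equal arms, which dropout does not guarantee. Section 12.2 also removes patients with LDL above 100 mg/dl at 4 months from the analysis, a further reason the arms may differ. One lost patient roughly halves the typical gain. That stands too, though the gain never turns negative.

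Third, the patients are selected as uncomplicated and low risk, so several of these events may be rare. At an assumed 5% v 15% with 27 per arm, power is 7.0% with Fisher and 14.1% with Boschloo. Neither is informative, and for such outcomes the change of test matters little in practice.

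Finally, the plan names SPSS 22 as well as R. The replacement is proposed for R only, a small practical cost.

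**Conclusion.** The point holds as a missed efficiency in secondary between-arm yes/no comparisons. Fisher's true size is at most about 2.6 to 2.8% with equal arms of 26 to 30, typically about 3.6 to 3.7% with slightly unequal arms, and lower still when events are rare. For assumed differences of 30 to 35 percentage points, Boschloo's test adds about 4 to 10 points of power with equal arms. With unequal arms it adds mostly about 1 to 7, with single cases below 1 and up to 9.1. The enumeration is exact, but the event rates and final arm sizes are assumptions.

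A reader might infer four stronger things that the protocol does not support:
- That the trial as a whole loses power. The primary variable is quantitative, and the 95% refers to it alone.
- That every yes/no analysis is affected. Within-arm comparisons use McNemar's test.
- That return to work is at risk. Section 7.3 and the month-4 and month-10 forms record it in days, so it goes to the t-test or Mann-Whitney test. Only the separate active-worker item is yes/no.
- That a gain near 10 points can be counted on. It belongs to equal arms and particular rates.

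**What to change.** In sections 1.15 and 9.3, replace Fisher's test for between-arm dichotomous comparisons with Boschloo's unconditional exact test (two-sided, run in R), reported with an exact unconditional confidence interval for the risk difference. Name the interval method, so that test and interval do not appear to disagree. Leave the McNemar tests and the tests for quantitative variables as they are.

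The cost is one sentence in each section and the use of R for these comparisons. It needs no extra patients or data, and the 5% limit and the exact-p rule are kept. The change should be fixed before anyone has seen yes/no outcomes by arm. If they have been seen, keep Fisher's test as the prespecified analysis and give Boschloo's result as a labelled sensitivity analysis.

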## Variables

1. Principal Variable

Since the main objective is adherence to a physical activity program, the main variable of the study is the METS-minute/week measure. Obtained from the IPAQ questionnaire.

1. Secondary variables

1. Clinical data: age, sex, STEMI, NSTEMI, unstable angina, stable angina, number of vessels, number of stents, complete revascularisation, active smoking, former smoker, hypertension, dyslipidaemia, diabetes mellitus, left ventricular ejection fraction, beta-blockers, ACE inhibitors/ARBs, statins, dual antiplatelet therapy.

2. Socio-occupational data: active worker, days until return to work after discharge.

3. Physical examination: systolic blood pressure, diastolic blood pressure, heart rate, body mass index (BMI), waist circumference, hip circumference.

4. Exercise test: VO2max, exercise time, maximal heart rate, maximal blood pressure, recovery time, ST decline, angor.

5. Pulse wave velocity.

6. Analytical data: glucose, creatinine, total cholesterol, LDL cholesterol, HDL cholesterol, triglycerides, CRPus, HbA1c.

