## Economic evaluation: cost-effectiveness analysis

The study includes a cost-effectiveness analysis to assess the costs and impact on health-related quality of life of the telerehabilitation intervention compared to in-hospital rehabilitation and the control group. The cost analysis will be carried out from the funder's perspective, including direct health care costs (pathology-related emergency visits, hospitalisations for the same cause, diagnostic and therapeutic tests such as revascularisations...) during follow-up. It will also include the costs derived from the intervention, which in the case of conventional rehabilitation, the programd schedule includes 16 rehabilitation visits, 8 rehabilitation sessions (with a physiotherapist, a nurse and a nursing assistant per session) and 8 educational talks. In the telerehabilitation group, the schedule includes 4 rehabilitation visits, 3 sessions (with a physiotherapist and a nurse) and 4 educational sessions. Unscheduled visits and sessions during the follow-up will also be included. The unit costs will be obtained from the Generalitat Valenciana catalogue.

Additionally, an analysis will be performed from a social perspective, including also indirect health care costs due to lost productivity of the patient (number of sick leaves and time to return to work after the event). Indirect costs will be reported by the patient in the follow-up data collection logbook. Effectiveness will be assessed by the physical activity performed by the patient, reported by the patient at the end of the follow-up, measured in METs-minutes/week.

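### The general test rule in section 9.3 does not exempt cost per patient/month, so its natural reading compares a skewed cost by Mann-Whitney ranks, which say little about mean cost

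*Protocol*

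**What the plan says.** Section 9.3, repeated in 1.15, covers "The comparison of the primary variable and the secondary variables of the study in both groups at baseline, at four months and 10 months". For quantitative outcomes the two-sample rule is "Student t-test for independent samples for quantitative variables (Mann-Whitney U test when parametric assumptions couldn’t be assumed". No criterion is given for deciding when the assumptions fail. The same paragraph plans multiple linear regression for the size and significance of the intervention effect.

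The secondary objectives (1.8 and 4.2) include "To evaluate the cost per patient/month in the control cases of conventional rehabilitation and extended tele-rehabilitation intervention".

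On the economic evaluation, 9.3 says only how prices are found: "For the economic evaluation, the unit cost will be obtained by quantifying the consumption of resources", with official rates applied. Section 9.4 sets the funder's perspective and adds a societal one. It lists the cost components: emergency visits, hospitalisations, revascularisations, the programme itself, and unscheduled visits and sessions. For conventional rehabilitation, "the programd schedule includes 16 rehabilitation visits, 8 rehabilitation sessions"; for telerehabilitation, "the schedule includes 4 rehabilitation visits, 3 sessions (with a physiotherapist and a nurse) and 4 educational sessions". It names no test or estimator for the difference in cost.

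**The concern.** A funder pays the total, so a comparison from the funder's perspective concerns mean cost per patient. Mann-Whitney asks whether a patient drawn from one arm tends to rank above a patient drawn from the other. When most patients have no event, that ranking is largely settled by the scheduled programme, which the protocol itself fixes. An admission counts as one high rank, whatever it costs.

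The p-value could then mostly restate the visit schedule and be nearly blind to whether later costs cancel the cheaper programme, which is what the cost analysis has to find out. The rank test and the cost-effectiveness result, which needs mean costs, could point in opposite directions. Cost containment is one of the possible advantages that the study rationale (section 3) wants estimated.

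**Working it through.** The protocol states no figure for the cost comparison, so there is nothing of its own to reproduce. It also gives no prices, event rates or cost SD; every such value below is an assumption.

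**Inputs from the protocol.** 16 v 4 scheduled visits (9.4); 27 analysed per arm and two-sided alpha 0.05 (9.1).

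**Step 1: constructed samples with equal mean cost.** Assume one cost unit per visit, so control costs lie just above 16 and telerehabilitation costs just above 4. Let k of the 27 telerehabilitation patients carry an extra cost of 12 × 27 / k each. That adds exactly 12 units to the arm mean and equalises the means.

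Those k patients rank above every control and the rest rank below. The Mann-Whitney statistic is therefore U = 27k, against 27 × 27 / 2 = 364.5 under the null, with SD = √(27 × 27 × 55 / 12) = 57.8.

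| k | Extra cost each | U | Exact Mann-Whitney p | t-test p |
|---|---|---|---|---|
| 1 | 324 | 27 | 1.5 × 10⁻¹¹ | 1.0 |
| 5 | 64.8 | 135 | 3.6 × 10⁻⁵ | 1.0 |
| 9 | 36 | 243 | 0.036 | 1.0 |

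For k = 9 the normal approximation agrees: z = (364.5 − 243) / 57.8 = 2.10. Every row favours telerehabilitation although the means are identical. Significance is lost at k = 10, where z = (364.5 − 270) / 57.8 = 1.63.

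**Step 2: simulation with equal true means, varying the programme gap.** Control cost = 4 + gap + N(0, SD 2) + event cost; telerehabilitation cost = 4 + N(0, SD 2) + event cost. Event cost = H × gamma (mean 1, CV 0.5), with H = gap / (difference in event probability) so that the true means are equal. For example, a gap of 12 with events in 10% v 20% gives H = 12 / 0.10 = 120. There are 27 patients per arm and 1500 trials per scenario. A gap below 12 represents a telemonitoring system cost that uses up part of the saving on visits.

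| Events, control v telerehabilitation | Gap | Mann-Whitney p ≤ 0.05 |
|---|---|---|
| 10% v 20% | 12 | 98% |
| 10% v 20% | 6 | 97% |
| 10% v 20% | 3 | 76% |
| 10% v 20% | 2 | 43% |
| 10% v 20% | 1 | 11% |
| 5% v 15% | 12 | 99.7% |
| 10% v 30% | 12 | 80% |

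At a 1-unit gap the three event settings give 6% to 13%; a repeat run gave 7% to 13%. At 10% v 20%, Welch's t-test on the same data rejected in 4.5% to 5.4%. Shapiro-Wilk rejected normality in at least one arm in 99% or more of trials at gaps of 2 or more, and in 62% to 99.5% at a gap of 1.

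**Step 3: a second cost model, gap fixed at 12.** Programme cost, plus gamma unscheduled use (mean 1, 4 or 12 units), plus lognormal event cost (CV 0.8), again with equal true means; 1000 trials per scenario. The check on equal means at 10% v 20% is 16 + 0.10 × 60 = 22 and 4 + 0.20 × 90 = 22. The table shows how often telerehabilitation is declared significantly cheaper.

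| Events, control v telerehabilitation | Mann-Whitney |
|---|---|
| 10% v 10% | 90–100% |
| 10% v 20% | 62–97% |
| 20% v 20% | 70–99% |
| 20% v 30% | 40–81% |
| 30% v 40% | 25–53% |
| 30% v 50% | 13–28% |

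Where event rates are equal, the telerehabilitation events are dearer. Student or Welch t gave about 3% to 17% in the same direction, highest when events are rare.

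**The case against.** A reader might infer that the protocol prescribes Mann-Whitney for cost. It does not. The rule is written for variables compared at baseline, four and ten months, whereas follow-up cost has no baseline value and section 6.6 schedules the cost-effectiveness analysis at ten months only. The objective is to evaluate cost, with no cost hypothesis, and cost has its own section. Section 7.3 does not list it among the secondary variables; the nearest item is "days until return to work after discharge". That omission carries little weight, because the diet and anxiety-depression scores are missing from the same list although diet and psychological state are secondary objectives. The other points stand: applying the rule to cost is the natural reading of the only two-sample rule given, not a stated instruction. With no normality criterion in the protocol, the Shapiro-Wilk check is illustrative only.

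The regression in 9.3 would give a mean-based estimate if applied to cost. It is not assigned to cost either, and it is described as adjustment for differences in patient characteristics, so it does not displace the two-sample rule.

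The estimator could be settled in the statistical analysis plan, which is not shown. Its absence from 9.4 is therefore not the point. The point is that the general rule, as written and without exemption, is unsuitable for this outcome, and an analysis plan that followed it would inherit the problem.

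A reader might also infer that a false saving is to be expected. The documents do not support that. It needs higher later costs in telerehabilitation, which nothing in them predicts; section 13.2 describes low-risk patients and minimal programme risks. The simulations impose that offset by construction. They cover neither a dearer telerehabilitation programme nor the societal perspective, where sick leave varies between patients and would loosen the link between ranks and the visit schedule.

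**Conclusion.** The concern holds as a weakness in how the general rule reaches cost. Section 9.3 gives one two-sample rule for quantitative secondary variables, cost per patient/month is a secondary objective, and no passage exempts it. Cost built from a near-fixed programme and occasional large events is likely to be strongly skewed, which points to Mann-Whitney. That test would mainly reflect the scheduled visits.

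If later telerehabilitation costs offset the cheaper programme so that means are equal, a saving is declared in about 7% to over 99% of trials. Rates are lowest when the programme gap is small and fall as events become common. The range rests on assumed visit-unit prices, event rates and between-patient spread. If later costs are similar in both arms and programme prices follow the visit counts, the saving is real and Mann-Whitney gets the direction right, though it still does not estimate its size.

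The point concerns a secondary economic objective and does not affect the METs-minutes/week comparison.

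**What to change.** - In 1.15 and 9.3, state that the Mann-Whitney fallback does not apply to costs.
- In 9.4, state that cost per patient/month is compared as the difference in arithmetic means with a 95% bootstrap confidence interval, resampling patients within arm.
- For the cost-effectiveness result, resample each patient's cost and METs-minutes/week together.
- Report median costs as description only.

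The cost is a wording change in three sections and a few lines of R, with no new data. The downside is a wide interval with 27 to 30 patients per arm, so a significant saving is less likely to be shown. Its coverage will be only approximate when events are rare. A plain t-test does not avoid that: in the second cost model it declared telerehabilitation cheaper in up to about 17% of trials with equal means.
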